## Processing of infrared thermographic images

The temperatures of specific acupoints (Dazhui, Zhiyang, Mingmen, Yaoyangguan, and tendon contraction) in the area of the Du meridian will be manually traced. Use SPSS 20.0 statistical software for analysis. Quantitative data is expressed as “mean ± standard deviation” (x ± s). If the data follows a normal distribution, paired sample t-test is used; if the data does not follow a normal distribution, non-parametric tests (Wilcoxon signed-rank test) are used. Skin temperature comparison before and after intervention at different acupoints in different groups is analyzed using one-way analysis of variance (ANOVA) if it follows a normal distribution and has equal variances. If the data follows a normal distribution but has unequal variances, Welch’s test is used. If the data does not follow a normal distribution, Kruskal-Wallis H test is used. *P* < 0.05 indicates statistical significance of the differences.

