### Secondary outcomes

#### Infrared image acquisition at the back along the governor vessel

Infrared images will be captured along the governor vessel of both groups of children: Healthy children and children with TD, aiming to identify any dissimilarities between these two groups. Additionally, infrared images will be captured in children with TD before and after the intervention, as for a comparative analysis.

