### Testing process

During the shooting process, the subject keeps the body upright, facing the camera with both upper limbs hanging down on both sides of the body. The infrared camera lens is 1 m to 2 m away from the subject, and the professional technician will take the picture, collect the infrared thermogram of the spine area and save the infrared image. Within the Du meridian area, specific meridian points such as Dazhui, Zhiyang, Mingmen, Yaoyangguan, and Jingsuo, will be manually traced. Afterwards, the computer automatically measure the average temperature of this area, record as t, and document the inspection results.

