## Statistical analysis

Descriptive statistical analysis, qualitative indicators are described by frequency table, percentage or composition ratio; Quantitative indicators are described by mean, standard deviation, or median, lower quartile (Q1), upper quartile (Q3), minimum value and maximum value.

The qualitative data are analyzed using the chi-square test, Fisher’s exact probability method, Wilcoxon rank sum test, CMH χ2 test, and WLS covariance. For the quantitative data, the normal distribution is verified using the t test (homogeneity test of variance is conducted between groups, with a test level of 0.05, and the Satterthwaite method is used for correction when the variance is uneven). For non-normal distribution, the Wilcoxon rank sum test and Wilcoxon signed rank sum test are employed, along with GLM covariance. A two-sided test is uniformly used for the hypothesis testing, and test statistics along with their corresponding P-values are provided, with *P* ≤ 0.05 indicating statistical significance and *P* ≤ 0.01 indicating high statistical significance.

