## Discussion

Currently, the clinical diagnosis of TIC disorder (TD) is primarily based on scale evaluation, which lacks of objective evaluation indicators and detection methods. However, there are metabolic differences in urine and feces between children with TD and healthy children. In order to further investigate the pathogenesis of TD, it is crucial to explore the urine and feces metabonomic analysis. In our preliminary study, our research discovered a distinct difference in the body temperature along the governor vessel between children with TD and healthy children: the heat distribution along the governor vessel of children with TD is in uneven state when compared to that of healthy children. Importantly, this uneven heat distribution is significantly improved after acupuncture treatment. Therefore, we hypothesize that this metabolic abnormality may be related to the changes of structure of infrared thermography of specific areas along the governor vessel and acupoints around it. Since currently, there is no effective diagnostic equipment for TD, so by fully utilizing the infrared thermal imaging technology and metabonomic analysis to further explore the underlying molecular mechanism by which changes of body temperature occur holds potential in identifying targets for future research purpose on the mechanism of acupuncture treatment aimed at regulating energy metabolism in children with TD.

This approach may also aid in the identification of micro-biomarkers associated with treatment outcomes and contribute to the development of a theoretical and experimental basis for diagnosing TD using infrared thermal imaging technology. However, this experiment has several limitations, including a small sample size, a long treatment cycle, low cooperation of children, and a potentially high dropout rate. Consequently, further studies with larger sample sizes, longer-term interventions, and comprehensive follow-up evaluations are needed.

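### Thermography is tested at five acupoints over several comparisons, each at P < 0.05, with no lead point, adjustment or exploratory label, so its familywise error is above 5%

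*Protocol article*

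**What the plan says.** Under *Processing of infrared thermographic images*, the protocol article lists what is measured: "The temperatures of specific acupoints (Dazhui, Zhiyang, Mingmen, Yaoyangguan, and tendon contraction) in the area of the Du meridian will be manually traced". *Testing process* gives the same list under slightly different names: "specific meridian points such as Dazhui, Zhiyang, Mingmen, Yaoyangguan, and Jingsuo, will be manually traced". I take the fifth item in the two lists to be the same point; the count is five either way.

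The processing section then fixes the tests. Paired data get a paired t-test or a Wilcoxon signed-rank test. For the rest, "Skin temperature comparison before and after intervention at different acupoints in different groups is analyzed using one-way analysis of variance (ANOVA"), with Welch's test for unequal variances and Kruskal-Wallis for non-normal data. It closes with the decision rule that P below "0.05 indicates statistical significance of the differences". The general *Statistical analysis* section adds: "A two-sided test is uniformly used for the hypothesis testing".

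The comparisons are set out under *Infrared image acquisition at the back along the governor vessel*. One is healthy versus TD children, "aiming to identify any dissimilarities between these two groups"; the other is before versus after treatment in TD children. The abstract lists thermography as a secondary outcome. The closing *Discussion* says that the approach may "contribute to the development of a theoretical and experimental basis for diagnosing TD using infrared thermal imaging technology".

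None of these sections names a main acupoint, a summary measure across points, a main comparison, a post-hoc procedure or a multiplicity adjustment. None calls the acupoint tests exploratory.

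**The concern.** Five points tested at 0.05 each, over more than one comparison, give a family of tests whose overall error rate is above 5%. Nothing in the text says which result would count as the thermography result. A search for any dissimilarity, with a significance label available at every point, leaves the choice of what to report until the data are seen.

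This is more than a detail left to another document. The article gives thermography its own analysis section, with software, test selection and threshold. Followed as written, that section allows a difference at any one acupoint to be called statistically significant.

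What is at stake is the reading of a secondary outcome that the authors hope will help support the diagnosis of TD by infrared imaging. The primary YGTSS comparison is outside this family, and its error rate does not change.

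**Working it through.** **The plan's own figure.** No familywise error rate is stated for thermography, so there is nothing to reproduce. The sample size rests on effectiveness rates of 95% and 55%, not on temperature. It supplies only the group size of 30 used below.

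**Inputs from the article**
- Acupoints per comparison: 5 (*Processing of infrared thermographic images*).
- Level per test: 0.05 (same section), two-sided (*Statistical analysis*).
- Comparisons: healthy versus TD; before versus after in TD children; across groups.
- Children per group: 30.

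**Assumptions, because the article does not say**
- The tests are run separately at each acupoint.
- Between-point correlation is varied from 0 to 0.9. Temperatures at points on one child's back are probably positively correlated, but no figure is given.
- Pre-post correlation is 0.6 where change enters.
- For the largest count, paired tests are done within each arm, and the across-group comparison is represented by a t-test of change between the two TD arms.

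**Step 1: independent tests.** The chance of at least one false positive among k tests is 1 − (1 − 0.05)^k.

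| k | Calculation | Result |
|---|---|---|
| 5 (one comparison) | 1 − 0.95^5 | 22.6% |
| 10 | 1 − 0.95^10 | 40.1% |
| 15 | 1 − 0.95^15 | 53.7% |
| 20 | 1 − 0.95^20 | 64.2% |

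**Step 2: correlated tests.** This is a simulation with no true effect, t-tests, 30 per group and 8,000 runs. The 20 tests are 5 paired tests in each of two arms (10), 5 between-arm tests of change, and 5 healthy-versus-TD tests at baseline. Data shared between comparisons are carried through.

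| Between-point correlation | One comparison, 5 tests | All 20 tests |
|---|---|---|
| 0 | 22% | 57% |
| 0.5 | 18% | 49% |
| 0.8 | 13% | 37% |
| 0.9 | 10% | 30% |

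A separate calculation with equicorrelated z tests (1,000,000 draws) agrees for one comparison: 0.227, 0.183 and 0.102 at correlations 0, 0.5 and 0.9.

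**Step 3: relative to the stated level.** For one comparison, 0.10/0.05 = 2 and 0.226/0.05 ≈ 4.5, so the error is about 2 to 4.5 times the nominal 5%.

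**Step 4: after adjustment within one comparison.** With five tests the Bonferroni level is 0.05/5 = 0.01. The simulated familywise error is then 4.9%, 4.4%, 3.2% and 2.4% at correlations 0, 0.5, 0.8 and 0.9. Holm's first step uses the same 0.01. When no effect exists at any point it therefore has exactly this error rate, and it is never less powerful than Bonferroni.

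**Step 5: two questions, each held at 0.05.** Jointly the error can reach 0.05 + 0.05 = 0.10, or 1 − 0.95² = 0.0975 if the two are independent.

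**The case against.** **It may sit in the full protocol or analysis plan.** A journal article need not carry every adjustment for a secondary outcome, and stating a 0.05 level does not exclude one. That is fair, and it limits the point to what is printed. But the article does print a rule for these tests. If an unseen plan adjusts, the published rule still needs to say so.

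**The number of tests is not fixed by the text.** This stands. The ANOVA sentence does not say whether the factor is group or acupoint, so an omnibus reading is possible. *Testing process* also has the computer record an average temperature for the area, which could mean one value instead of five. Point-level testing is the natural reading, because the analysis section speaks of specific acupoints and of different acupoints, but the test counts remain assumptions.

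**The purpose is hedged.** This also stands. The article speaks of exploring a possible mechanism, lists small sample size as a limitation, calls for larger studies and puts any guideline in the future. These hedges describe the aims; they do not attach an exploratory label to the acupoint tests, which keep their significance rule.

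**Two stronger readings.** A reader might infer that a chance finding is likely. For one comparison the figures do not exceed 23%, and they pass 50% only with roughly 15 to 20 tests that are independent or weakly correlated. A reader might also infer that one positive acupoint would be enough for a diagnostic claim. The article states no such rule. The pattern it describes is spatial: even heat in healthy children against a rising tendency in TD. One isolated point would not show that.

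**Conclusion.** The point holds as a moderate one about a secondary outcome. The thermography section applies P < 0.05 at each of five acupoints, over more than one comparison, without a lead point, an adjustment or an exploratory label.

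If the tests are run per acupoint, familywise error is about 10% to 23% for one comparison, for between-point correlations of 0.9 to 0. Over an assumed 20 tests it is about 30% to 57% in simulation, or 64% if all were independent. The single-comparison range is the firmer one, since it needs only the five points and a correlation. The 20-test range also rests on how the comparisons are counted.

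The primary YGTSS analysis is untouched. The documents support saying that the thermography error rate is uncontrolled as written. They do not support saying that a false finding is probable.

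**What to change.** In *Processing of infrared thermographic images*:

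1. Name two separate thermography questions: the randomised acupuncture-versus-sham comparison, and the TD-versus-healthy comparison at baseline. The first is not spelled out in the thermography text at present and should be. State that each is tested per acupoint, with group as the factor.
2. Within each question, report the five acupoints with Holm-adjusted P values at 0.05. Say plainly that error is controlled per question and not jointly over both.
3. Report all other acupoint comparisons, including within-group before-after changes, as exploratory, with estimates and confidence intervals and no claim of significance.

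The cost is one or two sentences and trivial computation. Power at any single acupoint falls slightly, since the smallest of the five P values must reach 0.01. The within-group before-after results also lose their significance label. The article reports that recruitment is under way, so the change should be dated and made before the thermography data are analysed.

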**Methods:**

This randomized controlled trial will recruit a total of 90 children, in which they will be divided into non-intervention group and intervention group. The non-intervention group consists of 30 healthy children while the intervention group consists of 60 children with tic disorder. The intervention group will be randomly allocated into either the treatment group or the control group, with 30 children randomly assigned in each group. Children either received acupuncture treatment and behavioral therapy (treatment group) or sham acupuncture treatment and behavioral therapy (control group), 3 treatment sessions per week for a period of 12 weeks, with a total of 36 treatment sessions. Outcome measures include YGTSS, urinary and fecal metabolomics, infrared thermography of body surface including governor vessel. For the intervention group, these outcome measures will be collected at the baseline and 90th day prior to intervention. Whereas for the non-intervention group, outcome measures (excluding YGTSS) will be collected at the baseline.

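### The thermography analysis names no acupuncture-versus-sham comparison, and its one-way ANOVA, read literally, can be significant when both arms change equally

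*Protocol article*

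**What the plan says.** The section on processing of infrared thermographic images sets out two families of tests.

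- Before versus after: "If the data follows a normal distribution, paired sample t-test is used", with the Wilcoxon signed-rank test when the data are not normal.
- Across groups, times and points: "Skin temperature comparison before and after intervention at different acupoints in different groups is analyzed using one-way analysis of variance (ANOVA", given normality and equal variances. The fallbacks are: "If the data follows a normal distribution but has unequal variances, Welch’s test is used" and "If the data does not follow a normal distribution, Kruskal-Wallis H test is used". The 0.05 level applies to all of these.

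The section on infrared image acquisition names two comparisons. One is healthy children against children with tic disorder (TD). The other is within TD: "infrared images will be captured in children with TD before and after the intervention, as for a comparative analysis". Acupuncture against sham is not named in either section.

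Each child has five marked acupoints. Children with TD are imaged at baseline and week 12. Healthy children are measured once (abstract, Methods): "Whereas for the non-intervention group, outcome measures (excluding YGTSS) will be collected at the baseline".

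The general Statistical analysis section lists, for quantitative data, a t test with the Satterthwaite correction, rank tests and a GLM covariance analysis, and adds that "A two-sided test is uniformly used for the hypothesis testing". It gives no model and does not say which of these applies to temperature.

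**The concern.** The trial randomises 60 children to real or sham needling, and both arms receive behavioural therapy. Thermography is one of its two mechanistic outcomes. The randomised contrast is what separates an effect of acupuncture from season, growth, repeat measurement or the shared therapy.

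The ANOVA sentence names neither the factor nor the response. Taken at its word, it puts time, acupoint and arm into a one-factor test. A significant result then says only that some cells differ, perhaps because both arms warmed or because skin temperature varies along the spine. The paired tests respect the pairing but answer only whether an arm changed. The Discussion already reasons this way when it describes preliminary data as showing improvement after acupuncture.

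At stake is a mechanistic claim for acupuncture resting on a result that the sham arm might show equally.

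**Working it through.** **Inputs from the article.** 30 children per randomised arm and 20% dropout, so 30 × (1 − 0.20) = 24 completers per arm; two visits for TD children; five acupoints; two-sided 5% level. The article states no design figure for thermography, so there is none to reproduce.

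**Assumptions.** Temperature SD set to 1 at each visit; normal data; pre-post correlation ρ of 0.3, 0.5 or 0.7; one acupoint at a time. Results marked (sim) are simulated; the others use the noncentral t distribution, and simulation agrees with them to within about one percentage point.

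**Check 1: both arms shift by 0.5 SD, no acupuncture effect.**

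- *One-way ANOVA over the four arm-by-time cells.* Cell means are 0, 0.5, 0, 0.5. The between-cell noncentrality is 24 × 4 × 0.25² = 6, which for independent readings with 3 and 92 degrees of freedom would give 50% rejection. With the actual pairing it is 47% to 50% (sim).
- *Paired t test in the acupuncture arm.* The SD of change is √(2(1 − ρ)) = 1.183, 1.000, 0.775. Noncentrality is 0.5 × √24 / SD = 2.07, 2.45, 3.16. Rejection is 51%, 65%, 86%.
- *Between-arm ANCOVA at week 12 with baseline as covariate.* About 5% at every ρ (sim), as it should be.

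**Check 2: is ignored pairing the cause?** With no shift and no effect, the four-cell ANOVA rejects in about 4% of trials (sim), slightly below nominal. The 47% to 50% therefore arises because the omnibus hypothesis includes time, not because pairing is ignored.

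**Check 3: do acupoint differences alone trigger it?** Take 30 per arm, all 20 arm-by-time-by-acupoint cells, acupoint means stepping by an assumed 0.3 SD, and no effect of time or treatment. The one-way ANOVA rejects in 100% of trials (sim).

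**Check 4: the favourable reading.** Suppose a separate ANOVA is run at each acupoint and visit. At week 12 only the two randomised arms have data, so the test is a two-sample t test of acupuncture against sham. Under the equal shift it rejects in about 5% of trials (sim), so it is valid. For a true 0.6 SD effect in the acupuncture arm:

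- *Week-12 test without baseline:* noncentrality 0.6 / √(2/24) = 2.08; power 53%.
- *ANCOVA:* residual SD √(1 − ρ²) = 0.954, 0.866, 0.714; noncentrality 2.18, 2.40, 2.91; power about 56%, 65%, 81%.

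If the response is instead the change at one acupoint, the between-arm test is again valid. Its variance is 2(1 − ρ), against (1 + ρ)(1 − ρ) for ANCOVA, so with ρ below 1 ANCOVA is the more precise.

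**The case against.** The strongest defence is that the sentence is compressed rather than wrong. The preceding sentence covers before versus after by paired tests, so the ANOVA may be meant for comparing groups separately at each visit and acupoint: three groups at baseline and two at week 12. Each child then gives one value per test. This reading is coherent and cannot be ruled out. However, the text does not say it, the sentence refers to both times and several points together, and even this version leaves baseline unused.

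A reader might infer three stronger charges that the article does not support.

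- *That readings are treated as independent and the error rate is therefore badly inflated.* Stacking the five points would do this: with design effect 1 + 4 × r, where r is the within-child correlation between points, r = 0.4, 0.6 or 0.8 gives 2.6, 3.4 or 4.2, and a nominal 5% arm comparison has a true error of 22%, 29% or 34%. But the article nowhere says that the points are pooled, and ignoring pairing at one point is slightly conservative.
- *That the plan has no between-group or covariate-adjusted method.* The general Statistical analysis section lists both. It simply does not tie them to thermography, which has its own section.
- *That healthy children are put into a before-after ANOVA.* The article measures them at baseline only and gives them a separate comparison with TD children.

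It is also fair that thermography is secondary, and that a plan not shown may hold the model. That does not remove the point, because the article itself names a test, and the test as worded does not isolate the randomised effect.

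**Conclusion.** The concern holds in a limited form. The thermography sections name no acupuncture-versus-sham contrast, and the one test that spans groups is worded so that its factor and response are undefined. Under the literal reading, a shift common to both arms gives a significant result about half the time, and the within-arm paired test gives one more often still. Under the favourable reading the test is valid, but with the assumed 0.6 SD effect it gives up between about 3 and 28 percentage points of power (53% against 56% to 81%).

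These sizes rest on assumed shifts, effects and correlations; the direction does not. It would be wrong to conclude that the trial's main result is at risk: tic severity on the YGTSS is the primary outcome and this sentence does not touch it. The wording should be fixed, but it is not a fatal flaw.

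**What to change.** Reword the thermography section as follows.

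1. The treatment comparison is acupuncture against sham at week 12, adjusted for baseline temperature: an ANCOVA for each acupoint or, if the points are analysed together, one mixed model with child as a random effect.
2. Children with TD and healthy children are compared on baseline values only.
3. Within-arm paired t or signed-rank tests are descriptive and carry no claim about acupuncture.

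The cost is wording only. The data are already being collected, the sample size is unchanged, and SPSS, which the article already names, fits these models. Recruitment is ongoing, so the change can be made and dated before database lock and unblinding.

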## Discussion

Currently, the clinical diagnosis of TIC disorder (TD) is primarily based on scale evaluation, which lacks of objective evaluation indicators and detection methods. However, there are metabolic differences in urine and feces between children with TD and healthy children. In order to further investigate the pathogenesis of TD, it is crucial to explore the urine and feces metabonomic analysis. In our preliminary study, our research discovered a distinct difference in the body temperature along the governor vessel between children with TD and healthy children: the heat distribution along the governor vessel of children with TD is in uneven state when compared to that of healthy children. Importantly, this uneven heat distribution is significantly improved after acupuncture treatment. Therefore, we hypothesize that this metabolic abnormality may be related to the changes of structure of infrared thermography of specific areas along the governor vessel and acupoints around it. Since currently, there is no effective diagnostic equipment for TD, so by fully utilizing the infrared thermal imaging technology and metabonomic analysis to further explore the underlying molecular mechanism by which changes of body temperature occur holds potential in identifying targets for future research purpose on the mechanism of acupuncture treatment aimed at regulating energy metabolism in children with TD.

This approach may also aid in the identification of micro-biomarkers associated with treatment outcomes and contribute to the development of a theoretical and experimental basis for diagnosing TD using infrared thermal imaging technology. However, this experiment has several limitations, including a small sample size, a long treatment cycle, low cooperation of children, and a potentially high dropout rate. Consequently, further studies with larger sample sizes, longer-term interventions, and comprehensive follow-up evaluations are needed.

